### Cluster formation and randomisation

The study will include 21 clusters randomised to three arms (7 clusters each) and allocated by a 1:1:1 ratio. While deciding the allocation ratio of 1:1:1 we considered the number of children with CP available in the BCPR sampling frame as well as the high mortality rate among children with CP below five years of age [37]. Each cluster will come from a ‘Mouza’, the smallest public administrative unit in Bangladesh comprising of approximately five villages (~8,250 people) and will include 10 CP child-primary caregiver dyads. In order to minimise ‘contamination’ of the intervention types, clusters will be separated from each other by buffering areas comprising villages not taking part in the study. Cluster margins will be configured so that they align with natural divisions that separate residents in the community (e.g. rivers). The randomisation process will be executed following the standard process.

### Blinding

The interventions will be open to participants and investigators, however, the outcome assessments will be observer blinded. An independent team, informed on the purpose and importance of blinding for this study, will conduct outcome assessments. The assessors will be masked/blinded about the interventions and the outcome assessment questionnaire will be designed in a manner that does not disclose the intervention.

### Intervention

#### Arm A- Integrated Microfinance/livelihood and Community-Based Rehabilitation (IMCBR)

Participants randomised to IMCBR arm will be supported to create microfinance/livelihood groups (10 CP child-primary caregiver dyads per group). The groups will be formed voluntarily along geographical boundaries to facilitate participation, retention, and meeting logistics. Each cluster will meet weekly to discuss microfinance/livelihood activities (e.g. weekly credit collection and troubleshooting) (90 minutes) and for CBR with children with CP comprising early intervention and primary caregiver’s education (90 minutes).

*A*.*1 Microfinance/livelihood program details*. Group meetings will be organised with members of each cluster to discuss (i) details of the program, (ii) potential benefits and challenges of participation in the program, and (iii) motivations for participation. Participants of each cluster can then apply for a loan/livelihood support; a minimum 10% deposit of the requested loan/livelihood support amount in the form of savings is required and is admissible immediately after cluster formation. Once the application is completed, loan approval and disbursement of the loan will occur approximately within one week. The loan disbursement and collection of repayment will be managed by a local microfinance organisation. However, the funds required for the loan will be reimbursed from the study budget at the end of loan disbursement.

Amount, return cycle of loan and investment areas: Each of the ultra-poor families will receive a loan/livelihood support amounting/equivalent to ~100–300 AUD at a 12% flat interest rate. The return cycle will be one year with a weekly repayment schedule. Common investment areas for the ultra-poor loan will be for goat or cattle rearing, seeds for agriculture, home-based weaving, and handicraft business [38].

*A*.*2 CBR*. There will be two major components of the CBR program, which will occur during cluster meetings following the microfinance/livelihood portion.

a. Goal Directed Training (GDT): Community-based GDT focused on motor learning will be conducted with children with CP and their primary caregivers. GDT is an activity-based approach to therapy where meaningful, client-selected (i.e. caregivers of children with CP) goals are used to provide opportunities for problem solving and to indirectly drive the movements required to successfully meet task demands [39]. Evidence from a meta-analysis showed that GDT based interventions are highly effective and should be the gold standard treatment for CP [40]. In this study, GDT will be delivered by child’s primary caregiver (participating parent). There are less than 10 rehabilitation professionals per 1 million population in Bangladesh and the majority of them are located in urban cities [41]. In absence of adequately trained professionals, parents-led early intervention strategies have been found very effective and been proposed in earlier studies including RCTs [42]. Parent training is vital as they are the only person who can identify a child’s self-initiated attempts and therefore can practice active motor tasks [43].

There will be four components of GDT;

Goal selection: The CBR session will start with realistic and appropriately time-framed goals set up in collaboration with parents. Goals are basically some specific tasks that are needed for everyday life and which children with CP find challenging. These tasks could be gross motor, self-care, communication, play, or school-based activities.Assessment: A detailed assessment will then be carried out to identify facilitating and limiting factors in achieving the goals. This will involve assessing the physical requirements of the selected task, the resources and equipment that are needed, and the settings in which the task is done. Both goal selection and assessment session will be facilitated by an experienced physiotherapist.Intervention: Weekly group therapy sessions will be conducted by two Community Rehabilitation Officer (CROs). The CROs hold a certificate level course on basic CBR techniques and have five years of experience in community-based management of children with CP. The CROs will guide parents/primary caregivers to scaffold the selected motor tasks, so that the child could actively complete at least a part of the task. Parents will be encouraged to use their knowledge of their child’s play preferences to elicit self-generated motor activity. Modified constraint induced movement therapy and/or bimanual training will be used when asymmetrical hand function is evident. CROs will also assist parents to set up a motor-enriched play environment at home to promote child’s self-generated movements, exploration, and task success. Parents will be advised to practice through joyful play until the main goal is achieved.Outcome evaluation: CROs will evaluate the compliance to the intervention by weekly follow-up phone calls weekly and monthly home visits. The attendance to group sessions and compliance to intervention will be monitored daily by a physiotherapist to ensure adherence to intervention. The extent to which a child’s goals are achieved will be monitored and recorded.

*b*. *Parents Training Module (PTM)*: Primary caregivers will participate in PTM to learn basic therapeutically correct skills for the day-to-day care and support of their child with CP embedded in the principles of GDT. This study will follow the PTM ‘Getting to know cerebral palsy’ which includes 10 modules and covers the following topics; introduction to CP, evaluating your child, positioning and carrying, communication, everyday activities, feeding your child, play, disability in your local community, running your own parent support group, and assistive devices and resources [44].

Specially trained CROs will facilitate each of the cluster meetings (both microfinance/livelihood and CBR activities). The CROs will facilitate microfinance/livelihood discussions and lead the GDT and PTM sessions with an aim to upskill primary caregivers so that they can continue to deliver GDT independently at home. Prior to implementation of the RCT, CROs will take part in a 5-day training by a Research Physiotherapist. The CRO training will cover the following areas; (i) socio-cultural considerations in working with primary caregivers of children with CP, (ii) introduction to microfinance/livelihood support program management, (iii) developmental milestones and development in children with CP, (iv) therapeutic principles, (v) GDT, (vi) activity focused therapies, (vii) basic speech development strategies, (viii) contraindications of therapies, (ix) research ethics, and (x) child rights.

#### Arm B- CBR alone

Participants from clusters randomised to this arm will attend a weekly rehabilitation session at a local focal point (preferably one of the group members’ homes). Each session will last for 90 minutes and will be identical to the CBR component of IMCBR (discussed above); however, the microfinance/livelihood component will not be provided.

#### Arm C- care-as-usual (i.e. no intervention)

This group will not receive any active intervention. Once children with CP are identified and randomised into clusters, the ‘care-as-usual’ participants will be provided with basic education on early intervention and rehabilitation and will be encouraged to access healthcare via usual routes, which typically include treatment in government hospitals. The proposed intervention schedules for all three arms have been summarised in S1 Table.

### Concurrent interventions

Children with CP from all three study arms will be able to continue accessing need-based medical and therapy support from other sources as per their family’s preferences. Frequency and duration of access to local medical/therapy services will be recorded during follow-up assessments and included in analysis.

### Outcome measures

The following outcomes will be measured at baseline, 6 months, 12 months, and 18 months.

### Primary outcomes

1. Health-related quality of life (HRQoL) of children with CP

*TNO-AZL Preschool children Quality of Life (TAPQOL)*: The TAPQOL is a validated tool designed to measure the parent perceived (i.e. proxy-reported) HRQoL of preschool children [45, 46]. The multidimensional instrument covers four domains; (a) Physical functioning, (b) Social functioning, (c) Cognitive functioning, and (d) Emotional functioning. The tool contains 43 items covering 12 scales (the number of items per scale ranges from 3 to 7), with higher scores indicating better HRQoL.

### Secondary and exploratory outcomes

1. Motor function of children with CP

*Gross Motor Function Measure (GMFM)-66*: The GMFM-66 is designed to assess the gross motor function in children with CP and measure changes over time. It is a valid and reliable tool comprising 66 items, subset of the 88 items included in original GMFM-88 developed based on the Rasch analysis to define the “gross motor function” of children with CP [47, 48]. The 66 activities in GMFM-66 cover five dimensions; (a) lying and rolling, (b) sitting, (c) crawling and sitting, (d) standing, and (e) walking, running and jumping.

*Gross Motor Function Classification System (GMFCS)*: The GMFCS is a five-level classification of functional motor abilities of children with CP. The Level I indicates minimal functional deficits among children with CP, whereas the level V indicates the highest level of functional deficits among children with CP [49].

*Classification of CP based on motor function and topographical distribution*: The predominant motor type i.e. spastic CP and non-spastic CP (dyskinesia, ataxia and hypotonia) and topographical distribution i.e. monoplegia, hemiplegia, diplegia, triplegia, and quadriplegia will be assessed following the BCPR protocol [3].

2. Communication function of children with CP

*Communication Function Classification System (CFCS)*: The CFCS is a validated tool to categorise children’s communication skills into five mutually exclusive levels of everyday communicative function. Classifications are made according to the descriptions of the levels and the distinctions between them [50, 51].

3. Nutritional status of children with CP

Anthropometric measurements will be taken using standard guidelines of WHO and will be analysed to assess the nutritional status of children. The following measurements will be collected at each assessment; (a) weight in kilograms, (b) height in centimetre (cm), (c) mid-upper arm circumference in cm, (d) skin-fold thickness in millimetre, and (e) head-circumference in cm.

4. Mental health of primary caregivers of children with CP

*Depression*, *Anxiety*, *Stress Scale–Short Form -21 (DASS-21)*: The DASS-21 is the shortened version of the DASS to assess symptoms of depression, anxiety and stress among adults. There are 21 items in this scale with four response options: 0 “Did not apply to me at all–Never”, 1 “Applied to me to some degree, or some of the time–Sometimes”, 2 “Applied to me to a considerable degree, or a good part of time–Often”, and 3 “Applied to me very much, or most of the time–Almost always” [52]. The Bengali version of the DASS-21 was previously validated to measure depression, anxiety and stress level among adults [53].

5. Health-related quality of life (HRQoL) of primary caregivers of children with CP

*Short Form 12-Version 2 (SF 12v2)*: The SF-12 is a validated tool to measure self-reported HRQoL of adults [54]. The tool has been widely used and has been translated into Bengali. In this study, we will use the reliable and validated Bengali version of the original SF-12 i.e. SF 12V2 [55]. The tool contains 12 questions covering eight domains; (a) physical functioning, (b) role physical, (c) bodily pain, (d) general health (e) vitality, (f) social functioning, (g) role emotional, and (h) mental health.

6. Social capital of primary caregivers of children with CP

*Short version of Adapted Social Capital Assessment Tool (SASCAT)*: The tool measures structural and cognitive social capital of the participants. The structural social capital is assessed based on responses on the following four domains (a) group membership, (b) support from groups, (c) support from individuals, and (d) collective action. The cognitive social capital is assessed based on following two domains; (a) trust and (b) social cohesion [56]. The SASCAT has been formally translated and validated into Bengali [57].

7. Family socio-economic status and food security

*Family income and expenditure*: Monthly family income and expenditure (as reported by the respondent) will be documented to measure the changes during the study period.

*Housing characteristics and household asset score*: A subset of the Bangladesh Demographic and Health Survey (BDHS) household questionnaire will be adopted to measure household wealth index of the participants. The BDHS is a nationally representative survey conducted every four years by the Government of Bangladesh in collaboration with the National Institute of Population Research and Training, Mitra and Associates and the United States Agency for International Development (USAID). This tool covers information on household ownership of a number of consumer items, ranging from a television to a bicycle, as well as housing characteristics, such as sources of drinking water, sanitation facilities, and type of material used for flooring, wall and roof [58].

*Household Food Insecurity Access Scale (HFIAS)*: The HFIAS tool (developed by the USAID) will be used to measure the household food insecurity level. HFIAS primarily focuses on “occurrence of food insecurity” followed by the frequency of the “occurrence of food insecurity” at the household level. The tool has nine questions and covers three domains of food insecurity (access); (a) anxiety and uncertainty about the household food supply, (b) Insufficient quality of food, and (c) insufficient food intake and its physical consequences [59]. Higher HFIAS score indicates higher food insecurity level.

*Food Consumption Score (FCS)*: The FCS tool (developed by the World Food Programme) will be used to assess dietary diversity at the household level. The tool has nine major food groups, a higher score indicates better quality of diet.

### Statistical methods

Data will be collected using paper-based forms. Research data will be anonymised and stored securely and separately for participant identifiable information. This will include monitoring secure data transfer from field to central office, data entry and quality control of completed forms, query about missing or invalid data and archiving of physical forms. Data will be collected using validated questionnaires. Data will be entered using Microsoft Access or SQL Server as the relational database engine. Any error identified during data entry or in data cleaning will be logged for field supervisor assessment and will be resolved after proper field verification. The physical data will be stored for seven years in a locked cabinet at head office of CSF Global based in Bangladesh as per national and international guidelines.

For statistical analysis, we will import the dataset into Stata 17. Primarily, we will perform an intention-to-treat analysis. Since our primary endpoint (i.e. HRQoL) will have continuous data, we will perform a mixed effect model (e.g. generalised linear mixed model) to calculate the effect of intervention according to the components of TAPQoL. We will also compare the TAPQoL scores between the three arms, and assess the differences using appropriate tests. Our proposed models will include the intervention arm as a fixed effect and study samples in each cluster as a random effect to explain cluster effects. To account for the intra-cluster correlation in calculating 95% CI and p-value, we will use a Sandwich estimate of standard error.

Baseline characteristics will be compared (as part of data matching) and adjusted using appropriate regression models. Descriptive statistics (frequencies, means and 95% confidence intervals) will be used to describe the sample at baseline and post-intervention. All analyses will be conducted using a significance level set at p<0.05. Data visualisation will be done using R Studio version 4.1.0.

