### Hypothesis

We hypothesise that compared to care-as-usual and CBR alone, the IMCBR program will be more effective in improving HRQoL, motor function, communication, and nutritional outcomes of children with CP from ultra-poor families; and the mental health, HRQoL, and social capital of their primary caregivers; and overall improvement in SES of the ultra-poor families of children with CP in rural Bangladesh.

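### The single primary outcome is analysed component by component at p<0.05, with no lead score, visit or success rule, so the false-positive rate of a primary claim is uncontrolled

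*Protocol article*

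**What the plan says.** The relevant statements are spread over five sections of the protocol article.

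- **Primary outcomes** lists one instrument: "The TAPQOL is a validated tool designed to measure the parent perceived (i.e. proxy-reported) HRQoL of preschool children". It has four domains (physical, social, cognitive, emotional), and "The tool contains 43 items covering 12 scales". No total score, lead domain or lead scale is named.
- **Statistical methods** says that the mixed model will be used "to calculate the effect of intervention according to the components of TAPQoL". It continues: "We will also compare the TAPQoL scores between the three arms, and assess the differences using appropriate tests". It also states: "All analyses will be conducted using a significance level set at p<0.05".
- **Outcome measures** says: "The following outcomes will be measured at baseline, 6 months, 12 months, and 18 months". No section names a primary visit.
- **Hypothesis** says that "compared to care-as-usual and CBR alone, the IMCBR program will be more effective". That gives two hypothesised contrasts, IMCBR vs care-as-usual and IMCBR vs CBR. A third, CBR vs care-as-usual, arises if all pairs of arms are compared.
- **Sample size calculation** predicts improvements in HRQoL of 35%, 20% and 5% in the three arms and claims 80% power at a two-sided 0.05. It treats HRQoL as one quantity.

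**The concern.** The trial is powered on one quantity at one significance level but analysed on several. A primary claim could rest on any component, on any pair of arms and, since no visit is named, on whichever visit is chosen. Each result would be judged at 0.05, and nothing in the text says which of them decides whether the trial succeeded.

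This matters for what follows the trial. The Introduction says that the implementing partner plans to scale up the program, in Bangladesh and elsewhere, if it proves effective. That decision needs one interpretable primary result. A program with no effect would have much more than a 5% chance of producing something that could be reported as a significant primary finding.

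**Working it through.** **The plan's own figures.** The plan states no family-wise error, so there is none to reproduce. Its nearest figure is 80% power at two-sided 0.05. The check did not reproduce that figure from the stated inputs, but this is a separate matter and nothing below depends on it.

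**Inputs from the article.** Components: 4 domains or 12 scales. Arms: 3, hence 3 pairs or 2 hypothesised contrasts. Follow-up visits: 3. Level per test: 0.05. Clusters per arm: 7.

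**Inputs assumed.** The article gives no correlations. Those between components were set at 0, 0.3, 0.5 and 0.7, paired with correlations between visits of 0, 0.5, 0.7 and 0.8.

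**Step 1: independent tests.** The chance of at least one false positive among k tests is 1 − 0.95^k.

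- 4 domains, one test each: k = 4, 1 − 0.95^4 = 18.5%.
- 4 domains × 3 pairs, one visit: k = 12, 46.0%.
- 12 scales × 3 pairs, one visit, or 4 domains × 3 pairs × 3 visits: k = 36, 84.2%.
- 12 scales × 3 pairs × 3 visits: k = 108, 99.6%.

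The three pairs share arms and are not independent, and components and visits will be correlated. Where several pairs or visits are tested, these are upper figures and Step 2 replaces them.

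**Step 2: simulation with no true effect anywhere.** There were 20,000 runs per setting, with 7 cluster means per arm, two-sided tests at 0.05, and variance pooled over the three arms: 3 × (7 − 1) = 18 degrees of freedom. Entries are the percentage of null trials with at least one p<0.05.

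| Reading | component correlation 0 | 0.3 | 0.5 | 0.7 |
|---|---|---|---|---|
| 4 domains, 1 visit, one overall three-arm test each | 18.5 | 18.0 | 16.1 | 14.1 |
| 12 scales, 1 visit, one overall three-arm test each | 46.1 | 41.6 | 33.9 | 25.1 |
| 4 domains, 1 visit, 2 hypothesised contrasts | 31.0 | 29.3 | 26.3 | 22.6 |
| 12 scales, 1 visit, 2 hypothesised contrasts | 67.7 | 61.1 | 51.5 | 39.4 |
| 4 domains, 1 visit, 3 pairs | 39.5 | 37.2 | 34.4 | 28.8 |
| 12 scales, 1 visit, 3 pairs | 77.8 | 70.6 | 60.2 | 47.2 |
| 4 domains, 3 visits, 3 pairs | 77.8 | 70.6 | 59.6 | 49.0 |
| 12 scales, 3 visits, 3 pairs | 99.0 | 96.2 | 87.4 | 71.0 |

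Calibration: one score, one visit and one overall test gave 5.0–5.2%, as it should. One score at one visit gave about 9% for the two contrasts and 11.7% for three pairs.

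**Step 3: success defined as beating both comparators.** If both contrasts must reach 0.05, the pair adds no inflation and each component has an error of at most 5%. That maximum is approached when IMCBR clearly beats care-as-usual but adds nothing to CBR. Over four domains the error is then up to 1 − 0.95^4 = 18.5%. Such a rule removes the contrast multiplicity but not the component multiplicity.

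**The case against.** **A multiplicity rule is usual SAP material.** The article condenses a fuller protocol, and an SAP may exist. The blanket p<0.05 sentence does not say that results will be unadjusted, and it can coexist with adjusted p-values or a hierarchy. This stands in part. The absence of a named visit or contrast order would not be a finding by itself. What the article does fix is an effect for each component, a further three-arm comparison and 0.05 for everything, against a sample size built on one quantity. Followed as written, that combination does not hold the error at 5%.

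**A false-positive primary result is close to assured.** A reader might infer this by multiplying 12 scales by several contrasts by three visits. The documents do not support it. Components may equally mean the four domains. Separate tests at each visit are nowhere stated: the model described has arm as a fixed effect and cluster as a random effect, with no visit term. Figures of 96–99% need the 12-scale, three-visit, all-pairs reading with low to modest correlation.

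**A null program would very likely show several significant primary findings.** The formula gives the chance of at least one. Under independence, the chance of two or more, 1 − 0.95^k − k × 0.05 × 0.95^(k−1), is about 6% for k = 8, 12% for k = 12 and 34% for k = 24. It becomes likely (about 88%) only at k = 72, which is 12 scales × 2 contrasts × 3 visits, a grid the article does not state.

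**The hypothesis may require superiority over both comparators.** If so, the doubling for two contrasts disappears. This is a fair reading of the Hypothesis section, but the Statistical methods section ties no test rule to it, and Step 3 shows that the component problem remains.

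**Conclusion.** The concern holds in this form: the one primary outcome is analysed by component at a blanket 0.05, alongside a three-arm comparison, with no lead score, visit or success rule, while the trial is powered on a single quantity at a single 0.05. The family-wise error of a primary claim is uncontrolled.

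At one visit with all three pairs tested, it is about 29–40% for four domains or 47–78% for 12 scales. If all visits are tested as well, which is an inference and not the plan's text, it is about 49–78% or 71–99%. On a narrow reading, four domains with one test each, it is up to 18.5%.

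The ranges rest on assumed correlations and on a global null with seven cluster means per arm. The exact size depends on what the plan means by components. That the error exceeds 5% does not: it did so on every multi-component reading simulated, and under the both-required rule it can still reach 18.5%.

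**What to change.** Add one paragraph to the protocol or SAP before anyone sees outcome data by arm. Investigators are not blinded to allocation, so the date of that decision should be documented.

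1. **Visit.** Name one primary visit, for example 12 months, when the intervention ends.
2. **Quantity.** Name either one TAPQOL score with a justified scoring rule, or the four domains with Holm adjustment. The article describes no TAPQOL total score, so an ad hoc average of domains or scales should not be adopted without support for its validity.
3. **Success rule.** State either a fixed sequence at two-sided 0.05 (IMCBR vs care-as-usual, then IMCBR vs CBR only if the first is significant) or a requirement that both contrasts reach 0.05. With one score at one visit, either keeps the error at or below 5%.
4. **If four domains are kept, combine the two rules explicitly.** Under the both-required rule, take the larger of the two p-values in each domain and apply Holm to the four. Under the fixed sequence, a simple valid choice is to run it within each domain at 0.05/4 = 0.0125.
5. **Labels.** Make the remaining scales and visits, and CBR vs care-as-usual, secondary.

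**Cost.** Single-component results become supportive, and under the fixed sequence the second contrast can be claimed only if the first succeeds. With one score, the sequence takes no alpha from the first test. If either contrast alone were to count, Bonferroni at 0.025 each would raise the detectable difference by (2.241 + 0.842)/(1.960 + 0.842) = 1.10, or about 21% more sample for the same power. Keeping four domains costs more: at 0.0125 the factor is (2.498 + 0.842)/(1.960 + 0.842) = 1.19, or about 42% more sample (1.19² ≈ 1.42), although later Holm steps are less strict.

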### Sample size calculation

The sample size for this cluster RCT has been computed based on methods described in Donner et al. [36]. We made several assumptions from the existing knowledge about the study population while calculating the sample size for this cluster RCT. Specifically, our sample size calculation is balanced between a standard statistical power and a pragmatic study setting. Based on our pilot data and existing literature we predict a 35% improvement of HRQoL in the IMCBR group, 20% improvement in the CBR alone group, and 5% improvement in the care-as-usual group [9]. A homogeneous study population will allow us to balance randomisation considering intra-cluster correlation of 0.5 and coefficient of variation in cluster size of 0.5.

Based on the calculation, we will recruit seven clusters in each arm (allocating 1:1:1), and each cluster will consist of 10 children with CP- primary caregivers dyads totalling 21 clusters of 210 dyads. With a sample size of 210 dyads, this study will have 80% statistical power to detect these effects (two-sided α-value = 0.05). Power calculation took into account up to 20% sample attrition by the end of the trial.

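### With 7 clusters per arm, the sandwich standard error planned for the model's p-values and 95% CIs gives about 9% type I error per comparison as written, not 5%

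*Protocol article*

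**What the plan says.** The Statistical methods section of the protocol article plans a mixed-effects model for the continuous primary outcome (TAPQOL), with arm as a fixed effect and a random effect for cluster. It then says how uncertainty is computed: "To account for the intra-cluster correlation in calculating 95% CI and p-value, we will use a Sandwich estimate of standard error". It adds: "All analyses will be conducted using a significance level set at p<0.05". The sample size section likewise uses "two-sided α-value = 0.05".

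The number of clusters is fixed elsewhere. Under Cluster formation and randomisation: "The study will include 21 clusters randomised to three arms (7 clusters each"). Under Sample size calculation: "totalling 21 clusters of 210 dyads".

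The article names no small-sample correction, t or F reference, degrees of freedom, permutation test or cluster-level analysis. The same section also plans a comparison of scores between arms by tests that it does not specify. Those tests are not tied to the sandwich.

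**The concern.** A sandwich variance is justified as the number of independent clusters becomes large. Here each pairwise comparison rests on 7 clusters against 7. At that size two things go wrong, both in the same direction. The estimator is biased downward, because residuals around a fitted arm mean are too small. It is also noisy, so a normal critical value is too short.

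The model's p-values would then be too small and its 95% intervals too narrow, including for the primary outcome. The Introduction says that the implementing partner plans to scale up the program, in Bangladesh and in other countries, if it proves effective. A false positive would therefore have consequences.

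**Working it through.** **Inputs from the protocol article.** 7 clusters per arm and 21 in total; 10 dyads per cluster, or 8 after the 20% attrition allowed for; "intra-cluster correlation of 0.5 and coefficient of variation in cluster size of 0.5"; two-sided 5% level. The figure to check is the nominal 5%. The stated 80% power is not an input.

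**Assumptions.** Arm is the only fixed effect; for the exact calculation, clusters are of equal size. The reference distribution is not stated, so several are shown.

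**Step 1: bias.** With e the deviation of a cluster mean from its arm mean, the plain sandwich variance of an arm mean is Σe²/7². The unbiased value is Σe²/(7 × 6). The ratio is 6/7 = 0.857. With a G/(G−1) multiplier for 21 clusters it is 0.857 × 21/20 = 0.90.

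**Step 2: degrees of freedom.** A comparison of two arms uses 7 + 7 − 2 = 12.

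**Step 3: true size.** If c is the critical value used and f the ratio from step 1, the true two-sided size is P(|t₁₂| > c√f).

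| Reference and multiplier | c√f | True size |
|---|---|---|
| Normal, none | 1.960 × √0.857 = 1.815 | 9.5% |
| Normal, 21/20 | 1.960 × √0.90 = 1.859 | 8.8% |
| t on 18 df, none | 2.101 × √0.857 = 1.945 | 7.6% |
| t on 18 df, 21/20 | 2.101 × √0.90 = 1.993 | 6.9% |
| t on 12 df, full 7/6 correction | 2.179 × 1 = 2.179 | 5.0% |

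Coverage on the first two rows is 90.5% and 91.2%. The last row recovers the nominal 5%, which confirms that the excess comes from the bias and the reference distribution.

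**Step 4: simulation.** 20,000 null trials per setting: 21 clusters, mean size 10 or 8, size CV 0 or 0.5, random-intercept model with a cluster-level sandwich. The ICCs of 0.05 and 0.01 are assumptions, added to show the range.

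| ICC | Normal, plain | Normal, 21/20 | t18, plain | Bias-reduced (CR2), t12 |
|---|---|---|---|---|
| 0.5 | 9.3–9.7% | 8.6–9.1% | 7.5–7.8% | 4.9–5.2% |
| 0.05 | 9.2–10.4% | 8.6–9.7% | 7.5–8.5% | 5.0–5.6% |
| 0.01 | 9.2–10.8% | 8.6–10.0% | 7.5–8.7% | 4.9–5.7% |

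The result depends little on ICC or attrition. The number of clusters drives it.

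**Step 5: the two comparisons in the Hypothesis section.** In simulated cluster means (equal sizes, equal variances), the chance of at least one false positive is about 16% to 17% with the sandwich and a normal reference. With a valid 12-df test it is about 9%.

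**Step 6: interval width.** The valid interval is (2.179/1.960)/√0.857 = 1.20 times the plain one, or (2.179/1.960)/√0.90 = 1.17 times the one with the 21/20 multiplier.

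**The case against.** The strongest objection is that the words uncorrected and normal do not appear in the article. Bias-reduced estimators are also sandwich estimators, and an article may leave the variant and the reference distribution to a fuller document. This stands as a limit on the size: a reader might infer that the true error is certainly 9% to 10%, and the text does not support that. It does not remove the point. The article assigns the intervals and p-values to a large-sample estimator and fixes 7 clusters per arm, and the simple adjustments in the table still leave about 7% to 9%.

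Three other stronger readings also fail:

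- **That the sandwich causes a 20% to 22% chance of a false positive.** That figure is for all three pairs of arms. A valid 5% test already gives about 12% there through multiplicity alone, and the Hypothesis section states only two comparisons.
- **That every comparison in the trial is affected.** The additional unspecified tests between arms are not tied to this standard error.
- **That the sandwich is unnecessary because the model has a cluster effect.** The two intervention arms meet weekly in groups and usual care does not, so between-cluster variance may differ by arm. A robust variance protects against that; a model with one common cluster variance does not. If the integrated arm's between-cluster variance were 2 to 4 times that of the others (an assumption), a pooled test on 18 df would reject about 6.5% to 8.5% of the time for a comparison with that arm.

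**Conclusion.** The point holds for the model-based p-values and 95% intervals. As literally written, with a normal reference, the type I error per pairwise comparison is about 9% (8.8% with the 21/20 multiplier, 9.5% without). With a t reference on 18 df it is about 7% to 8%. The bias always favours declaring a difference. The result rests on 7 clusters per arm, arm as the only fixed effect and the absence of a stronger correction in a document not shown. A bias-reduced estimator with about 12 df would bring the error close to 5%, so the method should be named and not left to software defaults.

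**What to change.** Keep the mixed model and replace the sentence on the standard error with one of these:

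- **Robust route:** a bias-reduced sandwich (CR2 or Kauermann-Carroll type), clustered on the randomised cluster, with a t reference on Satterthwaite degrees of freedom (about 12 for a pairwise comparison). This also allows for between-cluster variance that differs by arm.
- **Model-based route:** REML with Kenward-Roger or Satterthwaite degrees of freedom. The random effects must match the visits analysed: cluster for a single visit; cluster, child and cluster-by-time if the baseline, 6-, 12- and 18-month visits are analysed jointly. A cluster intercept alone would not suit a joint analysis.

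As a sensitivity analysis, add a cluster-level t-test with unequal variances (about 12 df) for each comparison.

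The cost is a change of wording, with no change to design or data collection. Intervals become about 15% to 20% wider, and power is somewhat lower but correctly stated.
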